#### Preimplementation Strategies

Preimplementation strategies for both the intervention and control arms were used before the trial commenced. These strategies provided CFHS staff members within the Hunter New England region with information on the HB4HNEKids program and provided scope and context for the scale-up of the program. Co-design with CFHS, service managers, and public health practitioners was undertaken to determine what strategies would be useful in preparing CFHS for the HB4HNEKids program throughout the local health district.

The preimplementation strategies, as illustrated in (Multimedia Appendix 2 [26,38-41]), were consistent across the intervention and control and included:

Involve executive boards: executive endorsement or management support.Conduct educational outreach visits and assess for readiness and identify barriers and facilitators: sector-based information sessions, providing information on the pilot study and the proposed future of the program.Build a coalition: establishment of sector-based key contact.Make training dynamic: brief prerecorded (15 min) presentation for service staff, outlining the program and objectives of the scale-up trial and professional taster messages, which provided clinicians the opportunity to experience a sample of messages (n=13) that families receive during the first 6 months of the program.

#### Intervention: Clinician-Initiated (Opt-In) Model

The clinician-initiated (opt-in) model is based on the process used during the pilot program to support clinicians in connecting families to the program. As per existing health service procedures, CFHS receives a referral from public and private maternity services following the birth of a baby and discharge of the mother and child from the hospital [42]. Upon discharge, CFHS staff contact the parent (participants) via phone call or SMS text message to offer a 1 to 4-week health and development check. During this contact with parents, staff from one of the clinician-initiated CFHS offer HB4HNEKids as part of routine care. CFHS staff also confirm feeding status (ie, if the child was breastfeeding, mixed feeding, or formula feeding), child name, mother's mobile number, and “offer of service” (ie, yes, client refused, or unable to contact after multiple attempts). If a staff member is unable to determine the infant’s feeding status during the initial contact, they will locate the “infant feeding status” via the hospital discharge summary provided by maternity services.

Building on the pilot, a series of additional strategies to improve the process of enrolling parents to the HB4HNEKids program have been co-designed by an expert task group and are outlined in the logic model (Multimedia Appendix 2 [26,38-41]). Following the process used for the intervention design, the established task group used the literature and local expertise to identify and map barriers and enablers to implement a clinician-initiated model. The BCW and TDF were also used to develop implementation strategies [38]; strategies were mapped to the ERIC strategies [40] and defined using the AACTT framework [41].

#### Control: System-Initiated (Opt-Out) Model

The control was a system-initiated (opt-out) model. The selection of a system-initiated model was based on clinician feedback during the pilot phase and automates the connection of families to the program. This model requires minimal input from clinicians. As per existing health service procedures, health service data are generated when CFHS receives a discharge referral from public and private maternity services for a mother or baby following the birth of a baby to initiate usual care via CFHS. This health service data will be used to identify parents who meet the predefined eligibility criteria for the HB4HNEKids program and will also be used to initiate the commencement of program messages, resulting in families automatically receiving the program. Predefined eligibility criteria were developed with and approved by CFHS clinicians. Nonetheless, CFHS staff are encouraged to refer to the program content as a potential trigger for discussions when conducting usual care. As part of this model, clinicians may opt out families from the program if it is not considered appropriate. Families can also opt out themselves, using the established pathways that cease program delivery to a family (eg, via links provided in messages, via links on the program website, or directly through a request to CFHS staff).

### Data Collection Procedures and Measures: Primary Outcome

The primary trial outcome will be the reach and representativeness of the HB4HNEKids program at 4, 6, 12, and 18 months from the commencement of the scale-up phase. The reach of the program by the scale-up model (clinician-initiated vs system-initiated) will be explored. Reach will be defined as: the number of eligible parents that are receiving HB4HNEKids (assessed via project records) and the proportion of parents receiving the program, calculated by the number of eligible parents receiving HB4HNEKids (numerator), divided by the total number of parents eligible for the program (denominator), identified via electronic health service records.

Representativeness will be assessed by comparing the characteristics of the parents receiving HB4HNEKids via each scale-up model to those of the total sample of eligible parents or carers referred to CFHS during the 18-month trial period. Characteristics of eligible parents (collected via electronic health service records and “The Good for Kids Parent Collective”) include parental age, geographic location, highest level of education, employment status (before birth of child), first baby (yes or no), number of children, language spoken at home other than English, and Aboriginal and Torres Strait Islander status. Sample representativeness of parents receiving the HB4HNEKids program at baseline and those remaining engaged at 18 months from both scale-up models will be compared, as well as compared with characteristics representative of the wider Hunter New England population.

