##### Parents

The mHealth SMS text message program, HB4HNEKids, will be delivered to eligible parents or carers (from herein named parents) alongside usual face-to-face CFHS care. Parent eligibility criteria for both the intervention and control arms were developed in partnership with CFHS clinical leads, and include: (1) must be eligible to access CFHS located in the HNELHD; (2) must own a mobile phone with SMS capability (96%) [34]; (3) must have a baby who has been discharged from a hospital in the last 8 weeks; (4) had a length of hospital stay less than 45 days; (5) absence of complex social issues resulting in the infant needing out of home care; and (6) baby was born ≥32 weeks of gestation. Furthermore, CFHS clinicians can use their clinical judgment to exclude families from the program at any time based on unforeseen personal circumstances. Over an 18-month intervention period, it is expected that approximately 15,000 parents (ie, 10,000 per year) who are referred to CFHS will be exposed to HB4HNEKids. All eligible parents who are referred to CFHS will be included in the sampling frame and analysis. While this RCT is planned to 24-month follow-up, there is scope to longitudinally follow this cohort across the first 2000 days (until their child is 5 years of age) to explore several outcomes of interest.

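### Reach is read at calendar cuts with no minimum time since discharge, so cuts taken during recruitment can understate opt-in reach if opt-in enrolment lags behind opt-out

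*Protocol article*

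**What the plan says.** All references are to the protocol article.

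- **Timing.** Data Collection Procedures and Measures: Primary Outcome sets "reach and representativeness of the HB4HNEKids program at 4, 6, 12, and 18 months from the commencement of the scale-up phase". The clock runs from the start of scale-up, not from a family's own birth, discharge or referral.
- **Numerator and denominator.** The same section counts "the number of eligible parents that are receiving HB4HNEKids (assessed via project records" and takes the proportion "divided by the total number of parents eligible for the program (denominator), identified via electronic health service records". It does not say how long a family must have been eligible before it counts, or when records are extracted relative to the cut.
- **Eligibility.** Under Parents, the family "must have a baby who has been discharged from a hospital in the last 8 weeks". A family therefore enters at discharge and has an 8-week window.
- **Opt-in route.** Intervention: Clinician-Initiated (Opt-In) Model says: "Upon discharge, CFHS staff contact the parent (participants) via phone call or SMS text message to offer a 1 to 4-week health and development check". It continues: "During this contact with parents, staff from one of the clinician-initiated CFHS offer HB4HNEKids as part of routine care". One recorded result of the offer is "unable to contact after multiple attempts".
- **Opt-out route.** Under Control: System-Initiated (Opt-Out) Model, referral data "will also be used to initiate the commencement of program messages, resulting in families automatically receiving the program".
- **Dates.** Table 1 (Results) marks participant recruitment from Q4 2024 to Q4 2025. Its footnote places the primary assessments at 6 months (2025-Q2), 12 months (2025-Q4), 18 months (2026-Q2) and 24 months (2026-Q4).

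**The concern.** At any cut taken while families are still being referred, the denominator includes some discharged only days before. Whether such a family is already in the numerator depends on how fast its arm enrols. One arm needs a person to get through to the parent; the other runs from a data feed. If the first is slower, families still waiting for an offer are scored the same as families who declined or could not be contacted, and this happens more often in the opt-in arm.

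The resulting gap would favour opt-out, which is the direction hypothesised for reach in the Discussion (Principal Findings). With a cumulative denominator, opt-in reach would also seem to rise from one cut to the next while true uptake stayed constant. The primary cost-effectiveness measure is cost per percentage change in reach, so it would inherit the error if computed at an affected cut. Elsewhere the article ties engagement and the characteristics of parents who opt out to time since birth; the primary outcome has no such per-family anchor.

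**Working it through.** The document gives no enrolment lag, so there is no figure of its own to reproduce. The 65% and 9.8 points below are taken from its sample-size paragraph as yardsticks only; nothing here depends on the sample-size calculation.

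**Inputs from the document**
- True opt-in reach p = 65% and detectable difference 9.8 points, both stated for 18 months (Sample Size and Power Calculation).
- Cuts at 4, 6, 12 and 18 months. In weeks, on a 52-week year, T = 17.33, 26, 52 and 78.
- Enrolment window of 8 weeks (Parents).

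**Assumptions, not in the document**
- Referrals arrive evenly over time.
- The denominator is cumulative, as the wording on the total number of eligible parents suggests.
- L is the mean opt-in lag in weeks, with opt-out lag zero. L is thus a net lag.

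**Formula.** With even arrivals, the share of would-be enrollees still waiting at the cut is L/T. Observed opt-in reach is p × (1 − L/T), so the shortfall is 65 × L/T points.

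| Cut | T (weeks) | L = 0.5 | L = 1 |
|---|---|---|---|
| 4 months | 17.33 | 65 × 0.5/17.33 = 1.9 | 65 × 1/17.33 = 3.8 |
| 6 months | 26 | 65 × 0.5/26 = 1.3 | 65 × 1/26 = 2.5 |
| 12 months | 52 | 65 × 0.5/52 = 0.6 | 65 × 1/52 = 1.3 |
| 18 months | 78 | 65 × 0.5/78 = 0.4 | 65 × 1/78 = 0.8 |

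For a given lag, the 4-month shortfall is 78/17.33 = 4.5 times the 18-month one.

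**Longer lags.** The shortfall is proportional to L. A mean of 2 weeks gives 65 × 2/17.33 = 7.5 points at 4 months and 65 × 2/78 = 1.7 at 18. A mean of 4 weeks gives 15.0 and 3.3.

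**Lag in the opt-out arm too.** Take opt-out reach as 65 + 9.8 = 74.8% (assumed) with mean lag K. The error in the difference is (65 × L − 74.8 × K)/T.
- L = 2, K = 1: (130 − 74.8)/17.33 = 3.2 points at 4 months, and 55.2/78 = 0.7 at 18.
- L = K = 1: (65 − 74.8)/17.33 = −0.6 at 4 months, and −9.8/78 = −0.1 at 18. With equal lags the error is essentially gone and, if anything, slightly reversed.

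**Table 1's dates.** The 6- and 12-month assessments (2025-Q2 and 2025-Q4) fall in quarters marked for recruitment. The 18-month assessment (2026-Q2) comes at least one full quarter after the last marked recruitment quarter. That is longer than the 8-week window, so the shortfall there is close to 0.

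**Other reading of the denominator.** If only families currently inside the 8-week window were counted, the shortfall would be 65 × L/8, or 8.1 points per week of lag, equally at every cut while recruitment is open. The wording favours the cumulative reading but does not settle it.

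**The case against.** The strongest reply is that the lag may be trivial. Staff make contact upon discharge, and the program is offered during that contact, not at the later 1 to 4-week check. The Introduction has the program starting within days of birth. A reader might take the 1 to 4-week range as the enrolment delay and conclude that the 4-month artefact (9.4 points for a 2.5-week mean, 15.0 for 4 weeks) rivals the 9.8-point target. The documents do not support that: the range times the check, and the 9.8 points refer to 18 months. The category for failed contact attempts describes families never reached, so it does not time the successful contacts. This objection stands, and it is why the range used here is 0.5 to 1 week.

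Nor is the opt-out start shown to be instantaneous. Referral data must be screened for eligibility, and a team member generates and uploads the messages. Only the difference in lags matters. This also stands.

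Third, extraction dates and window rules are often left to a fuller document. That is fair as far as omissions go. But the article does fix the time points by calendar and the denominator as all eligible parents, and that combination creates the problem.

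Fourth, a slower start is a genuine feature of opt-in, so counting it could be a deliberate choice. In that case time to enrolment should be reported as such. A calendar cut weights it by how long recruitment has run, which says nothing about either model.

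A reader might also infer that representativeness is distorted. That has not been shown: families still waiting would have to differ in their characteristics from those discharged earlier, and nothing in the document suggests they do.

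**Conclusion.** The definition of the primary outcome allows a timing artefact. It runs against opt-in if, and only if, opt-in enrolment lags more than opt-out. The two enrolment routes make that plausible, but the document does not establish it, so opt-in reach can be understated; it cannot be said that it is.

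For a net mean lag of 0.5 to 1 week the size is modest: 1.9 to 3.8 points at 4 months, falling to 0.4 to 0.8 at 18. These figures rest on even referrals, a cumulative denominator, 65% true opt-in reach and records read at the cut. The 18-month comparison, which the sample size addresses, is barely touched, and on Table 1's dates hardly at all. The point matters for the 4-, 6- and 12-month readings, which the outcome section also makes primary. Table 1's footnote lists 6, 12, 18 and 24 months instead, so whether the most exposed cut, 4 months, is a primary reading needs to be reconciled.

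**What to change.** Define reach per family and identically in both arms: a family is reached if it was enrolled within 8 weeks of discharge. At each cut, include in numerator and denominator only families whose 8-week window has closed, and carry the rest to the next cut. This uses the protocol's own eligibility window and removes the artefact whatever the lags, provided enrolment happens inside the window. The same sentence should say how a family that enrols and then opts out within 8 weeks is counted. If speed of enrolment is of interest, report time from discharge to enrolment separately by arm.

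The cost is a sentence in the outcome definition and a logged modification, with no change to trial conduct. Discharge and enrolment dates should already be held for checking eligibility and sending messages. While recruitment is open, the rule drops the last 8 weeks of referrals at each cut: 8/17.33 = 46% at 4 months, 8/26 = 31% at 6, 8/52 = 15% at 12 and 8/78 = 10% at 18. For the early cuts it is better to keep every family referred up to the cut and read the records 8 weeks later, which costs only the delay. If recruitment closes in Q4 2025 and the 18-month reading is in 2026-Q2, that reading loses nothing.

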### Randomization and Blinding

Given that CFHS clinicians may work across multiple CFHS within a region or sector, the randomization for this trial will be conducted at the CFHS sector level to minimize possible contamination across CFHS sites. The 6 CFHS sectors (including 39 CFHS) will be stratified by geographic location and number of births/year (based on whether the number of births is higher or lower than average), and randomized in a 1:1 ratio to one of the 2 trial arms (clinician-initiated or system-initiated). Randomization will occur by an independent statistician using Microsoft Excel. CFHS will not be blinded to group allocation; however, the primary trial outcome—reach and representativeness of HB4HNEKids—will be objectively assessed via electronic records of service enrollment.

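### Reach is named as receiving the program but assessed from enrolment records, which could count undeliverable families as reached in the opt-out arm

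*Protocol article*

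**What the plan says.** **Endpoint.** Data Collection Procedures and Measures: Primary Outcome counts "the number of eligible parents that are receiving HB4HNEKids (assessed via project records") and forms the proportion as that count "divided by the total number of parents eligible for the program (denominator), identified via electronic health service records". It gives no rule for when a parent counts as receiving.

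**Measurement source.** Randomization and Blinding says that reach and representativeness "will be objectively assessed via electronic records of service enrollment".

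**Opt-in route.** Under Intervention: Clinician-Initiated (Opt-In) Model, staff contact the parent by phone or SMS, offer the program, confirm the mother's mobile number, and record the offer of service as "yes, client refused, or unable to contact after multiple attempts".

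**Opt-out route.** Under Control: System-Initiated (Opt-Out) Model, health service data generated by the discharge referral "will also be used to initiate the commencement of program messages, resulting in families automatically receiving the program". No step that checks the number is described.

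**Delivery.** HB4HNEKids SMS Text Message Program says that the SMS provider could not track read receipts. It is silent on delivery or failure reports. No section says how an undelivered message or an invalid number is classified in either arm.

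**The concern.** The endpoint's name refers to families who get messages, but its stated source is enrolment, and enrolment means different things in the two arms. An opt-in enrolment normally implies a recent contact and a confirmed number. An opt-out enrolment, as described, implies only that referral data met the criteria and messages were started. A family whose recorded number cannot take messages would tend not to be enrolled under opt-in, or would have the number put right. Under opt-out it would be logged as reached. Such a family never sees the message link for opting out, so it could stay in the numerator at 4, 6, 12 and 18 months.

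At enrolment the error would run towards opt-out, which the Discussion hypothesizes will have the greater reach. Reach also enters the primary cost-effectiveness measure, the incremental cost per percentage change in reach. Strengths and Limitations acknowledges that the opt-out model depends on good health system data. A numerator built on enrolment alone would record poor contact data as success.

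**Working it through.** **Inputs from the protocol article.** Sample Size and Power Calculation gives opt-in reach of 65% and a detectable difference of 9.8 points. Opt-out logged reach at that difference, in the hypothesized direction, is 65 + 9.8 = 74.8%.

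**Input not in the article.** The share *f* of logged opt-out families whose number is undeliverable. It is assumed here to be 1% to 10%. The 96% attached to the phone criterion under Parents is ownership, so its complement is not an estimate of *f*.

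**The plan's own figure.** The article gives no figure for misclassified reach, so there is none to reproduce. The 9.8 points serve only as a yardstick. The sample size stated for that difference, 1126 per arm, was not reproduced: without clustering, 65% against 74.8% needs 343 per arm, and the article states no cluster size from which to rebuild the rest. That is a separate matter and does not affect what follows.

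**Step 1: overstatement of opt-out reach.** With logged reach *R*, true reach is *R*(1 − *f*), so the overstatement is *f* × *R*. At *R* = 74.8%:

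| *f* | Overstatement (points) | True opt-out reach | True gap from 65% | Share of 9.8 |
|---|---|---|---|---|
| 1% | 0.7 | 74.1% | 9.1 | 8% |
| 2% | 1.5 | 73.3% | 8.3 | 15% |
| 5% | 3.7 | 71.1% | 6.1 | 38% |
| 10% | 7.5 | 67.3% | 2.3 | 76% |

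**Step 2: equal true reach.** If both arms truly reach 65%, logged opt-out reach is 0.65 / (1 − *f*). For *f* = 1% this is 65.7%, and for *f* = 10% it is 72.2%. The spurious difference is 0.7 to 7.2 points in favour of opt-out.

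**Step 3: cost per percentage point.** The gap in reach is the denominator. At *f* = 5% the logged gap of 9.8 stands for a true gap of 6.1, so the denominator is too large by a factor of 9.8 / 6.1 = 1.6.

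All three steps assume that enrolment is the counting rule, that undeliverable numbers occur independently of opting out, and that the opt-in count carries no matching error at enrolment.

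**The case against.** **The counting rule is partly inferred.** The outcome section says receiving, from project records. For engagement, the article describes project records as drawing on REDCap and the text message platform, so delivery data may already feed the count. The detailed rule may also sit in a fuller document. This stands as a possibility. It does not settle the point, because the only source the article names for the primary outcome beyond project records is enrolment, and the opt-out section equates initiation with receipt.

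**The contrast between arms is less clean than it looks.** The code "unable to contact after multiple attempts" would also cover working numbers that go unanswered. Opt-in contact may be by SMS. Opt-out families also have usual CFHS contact, where a bad number could surface, and clinicians can remove families. This stands and would reduce the size. No described step carries such a discovery into the reach count.

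**Other measures would help.** The article expects its evaluation to highlight data problems, and it measures click-through among eligible parents from 4 months. That helps expose non-receipt, but it is not a delivery count.

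**Stronger readings to resist.** A reader might infer that the endpoint is biased and always favours opt-out. The documents do not support that. Scoring an uncontactable opt-in family as not reached is correct, so any error at enrolment lies only in the opt-out numerator, and a number that dies later is miscounted in both arms. A reader might also take 10% undeliverable at 95% logged reach, a 9.5-point overstatement, as cancelling the target difference. In that case the logged gap from 65% is 30 points and 20.5 remain, so the comparison would not be overturned.

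**Conclusion.** The concern holds as a potential differential misclassification of unknown size. Followed as written, the article's stated source would count an opt-out family with an undeliverable number as reached, while the opt-in route would screen that family out or correct its number. The article gives no rate of undeliverable numbers, so 0.7 to 7.5 points is an illustration under an assumed 1% to 10% at 74.8% logged reach, and it applies only if enrolment is the counting rule. The documents do not establish that the primary comparison is in fact biased, nor by how much. They do show an endpoint whose name and stated source differ, in a trial where the difference matters more in one arm than in the other. Aligning the two is a worthwhile and inexpensive improvement.

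**What to change.** Define receiving identically in both arms: the parent is enrolled, has not opted out at the time point, and has at least one program message recorded by the SMS platform as delivered within a fixed window after enrolment. Report enrolled separately as a supporting measure, and state which of the two feeds the cost per percentage change in reach.

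Confirm first that the platform can export delivery or failure status; the article rules out read receipts only. If it cannot, exclude records with a missing or invalid-format number from the numerator in both arms, label the measure as enrolled and not as receiving, and state the limitation.

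The cost is a sentence or two in the outcome definition and a status export. The opt-out reach figure may fall somewhat. Delivery status will not detect a live number that belongs to someone else, so that limitation should be stated in either case. The definition should be settled before reach is tabulated by arm, so that it cannot look driven by the result.
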